#### Analyses of secondary outcome

Logistic regression will be used to evaluate the association between the individual components of the 16-question KICA, in its original and modified forms, and the presence of CIND and dementia diagnoses. Results will be reported as OR with 95% CI. This will allow for the identification of parameters in the KICA that are most sensitive for dementia. Sensitivity and specificity values and optimal cut-off scores will be informed by formulation of receiver operating characteristic (ROC) curves and area under the curve (AUC) calculations. Multivariable logistic regression will be used to adjust for the effect of potential confounding variables such as age, sex, education and study cohort. A resulting prototype short scale will then be validated in a separate cohort of Aboriginal and Torres Strait Islander peoples.

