### Study aims

The aim of this research is to elucidate risk factors associated with cognitive impairment and dementia by combining landmark cohort studies involving Aboriginal and Torres Strait Islander participants. The Kimberley Healthy Adults Project (KHAP), Koori Growing Old Well Study (KGOWS) and the Torres Strait Dementia Prevalence Study (TSDPS) share similar study methodologies and outcome measures that allow for harmonisation to examine both risk and protective factors of brain health and impairment in a larger combined cohort that may offer greater insights through enhanced diversity and statistical capability.

Primary outcomes:

Elucidate risk and protective factors associated with dementia and/or cognitive impairment in a combined cross-sectional dataset of Aboriginal and Torres Strait Islander participants.Elucidate risk and protective factors associated with incident dementia and/or cognitive impairment in a combined longitudinal dataset of Aboriginal and Torres Strait Islander participants.

Secondary outcomes:

Identify items in the Kimberley Indigenous Cognitive Assessment (KICA) or modified KICA (mKICA) that are most sensitive for dementia or cognitive impairment in the harmonised cross-sectional dataset.

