## Methods/design

### Design

The KHAP study was undertaken from 2004 to 2006 and involved 363 Aboriginal participants aged 45 and older from different communities in the remote Kimberley region of WA [1]. The KGOW study recruited 336 participants aged 60 and older from five Aboriginal communities, two from metropolitan Sydney and three in regional coastal areas of NSW between 2010 and 2012 [14]. Follow-up of participants occurred after six and seven years for KGOWS-II and KHAP wave 2, respectively. The TSDP study was conducted between 2015 and 2018 and recruited 274 participants aged 45 and older from five mainland and 18 island communities across the Torres Strait and Northern Peninsula [3]. A summary of the studies and number of participants is provided in Table 1. All three cohort studies worked in partnership with local community organisations and Aboriginal and Torres Strait Islander members and researchers to support recruitment, data collection, and feedback to communities to ensure culturally safe engagement with participants. Risk factors were collected using a structured interview protocol and encompassed demographic, medical, and psychosocial factors collected from participants and family carers where available. This comprehensive assessment was independently evaluated by a panel of clinical specialists to establish clinical diagnoses by consensus. All three cohort studies used the KICA, a screening tool for older Aboriginal and Torres Strait Islander peoples, that was validated in the remote Kimberley region of WA [15], modified for urban and regional dwellers in the form of the mKICA [16] and adapted for the Torres Strait [17]. A shortened version (KICA-Screen) has been validated for face-to-face and telehealth administration [17, 18].

**Table 1 Tab1:** Descriptive summary of landmark studies

Study/Cohort	Location	Age (years)	Sample Size (*N*=)	Participants (*n*=)
Kimberley Healthy Adults Project (KHAP)				
Wave 1 (W1) 2004–2006 [1, 8]	Remote WA	≥ 45	363	289 with normal cognition; 45 with dementia; 29 with CIND*.
Wave 2 (W2) 2011–2013 [9]	Remote WA	≥ 45	398‡	. Of 363 W1 participants, 184 completed all W2 assessments, 5 had cognitive assessment only, 109 had died and 65 declined to participate or could not be located. 105 new participants were recruited at W2. W2 cohort: 226 with normal cognition; 29 with dementia; 33 with CIND; 1 missing diagnosis; had 109 died.
Koori Growing Old Well Study (KGOWS)				

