#### Data harmonisation

Data will be harmonised using the Stata statistical package (StataCorp, College Station, Texas), version 17. Variables of interest will be recoded to be consistent across datasets prior to combination into a single final dataset. Data harmonisation utilises the best available information. This means that patient self-reports for a given variable may be corroborated by information from family reports, medications, primary care software derived medical history and medications where available. For instance, the variable diabetes combines self-reports of the condition (yes/no), family informant reports of the condition (yes/no), and medication history (diabetic medication by self-reports or in medication review). Medication lists available for the participants will be coded using the World Health Organization’s Anatomical Therapeutic Chemical (ATC) Classification and allow for sub-analyses of outcomes in relation to medication categories of interest such as anticholinergics, analgesics, anti-psychotics and so forth [33]. The full details of variables of interest in the pooled cross-sectional dataset are provided in the appendices (Appendix 1.1).

Based on the variables of interest available in each dataset (Table 2), KHAP wave 2, KGOWS-I and TSDPS will be harmonised in cross-section, with a combined cohort of 898 Aboriginal and Torres Strait Islander participants, 244 (27%) of whom will have a diagnosis of dementia or CIND/MCI. For longitudinal analyses, data from KHAP wave 1 will be harmonised with KGOWS-I and combined with diagnoses at baseline (wave 1) and follow-up (wave 2) for analysis of factors of interest in a smaller subset of 354 participants as summarised in the appendices (Appendix 1.2). There is no longitudinal data available for TSDPS at the present time.

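### The KICA item search pools three versions of the tool and handles cohort only as a confounder, so items that discriminate unevenly and a common cut-off that performs unevenly would go unseen

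*Protocol article*

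**What the plan says.** Under Design, the protocol article says the KICA was validated in the remote Kimberley and then "modified for urban and regional dwellers in the form of the mKICA [16] and adapted for the Torres Strait". That makes three versions, apparently one per cohort.

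Under Study aims, the secondary objective is to find the KICA or mKICA items "that are most sensitive for dementia or cognitive impairment in the harmonised cross-sectional dataset". Data harmonisation describes that data set, "with a combined cohort of 898 Aboriginal and Torres Strait Islander participants, 244 (27%) of whom" have dementia or CIND/MCI.

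Under Analyses of secondary outcome, logistic regression is applied to the "individual components of the 16-question KICA, in its original and modified forms". Multivariable regression is used to "adjust for the effect of potential confounding variables such as age, sex, education and study cohort". For accuracy, "optimal cut-off scores will be informed by formulation of receiver operating characteristic (ROC) curves". The end product is singular: "A resulting prototype short scale will then be validated in a separate cohort".

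The article mentions no analysis by version or cohort, no item-by-cohort term and no check that items are equivalent across versions.

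**The concern.** Confounder adjustment suits an association estimate. Choosing items and cut-offs for a screen to be used in different communities needs more, because discrimination has to hold in each version. A cohort main effect gives each cohort its own intercept but imposes one odds ratio per item. An item that works well in two cohorts and poorly in the third can then rank above an item that works adequately in all three. A total score or ROC curve formed without regard to cohort has no such intercept, so a version that is simply easier or harder shifts the sensitivity and specificity of a common cut-off in that community.

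At stake are which items enter the short scale, and whether the cut-off carried into validation misses cases in one community and over-refers in another.

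**Working it through.** **1. The plan's own figures.** Counts are from Table 1, omitting the one KHAP wave 2 participant without a diagnosis.

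| Cohort | N | Impaired | Not impaired | Prevalence |
|---|---|---|---|---|
| KHAP wave 2 | 226 + 29 + 33 = 288 | 29 + 33 = 62 | 226 | 21.5% |
| KGOWS-I | 249 + 45 + 38 + 4 = 336 | 45 + 38 = 83 | 253 | 24.7% |
| TSDPS | 175 + 39 + 60 = 274 | 39 + 60 = 99 | 175 | 36.1% |

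The totals are 288 + 336 + 274 = 898 and 62 + 83 + 99 = 244, and 244/898 = 27.2%. Both stated figures reproduce, with the four KGOWS participants who have another cognitive disorder counted as not impaired. Version is therefore associated with the outcome.

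The documents give no item-level or score data. Every shift, odds ratio and error rate in steps 2 to 5 is an assumption.

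**2. What the cohort main effect does and does not do.** These are expected-count logistic regressions of diagnosis on a binary item error, using the counts above.
- Same item OR of 6 in every cohort, with error rates among the unimpaired that differ by cohort: the crude pooled OR falls to between 4.2 and 5.5. Adding cohort restores 6.0. Pure difficulty differences are removed.
- 20% errors among the unimpaired and item ORs of 10, 2 and 10 (KHAP, KGOWS, TSDPS): the adjusted model reports a single OR of 5.6. An item with OR 5 in all three cohorts gets 5.0. The uneven item ranks higher although its OR in KGOWS is only 2.

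**3. One cut-off across versions.** Equal-variance normal scores are assumed. Sensitivity and specificity of 80% each mean z = 0.842 and a separation of 2 × 0.842 = 1.683 SD. If two versions differ by D and the common cut-off lies midway between their ideal cut-offs, one version has accuracies Φ(0.842 − D/2) and Φ(0.842 + D/2), and the other has them reversed.

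| D (SD) | One version, sens/spec | Other version, sens/spec |
|---|---|---|
| 0.25 | 76/83 | 83/76 |
| 0.5 | 72/86 | 86/72 |
| 1.0 | 63/91 | 91/63 |

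A second model uses a separation of 1.5 SD, a pooled cut-off maximising sensitivity plus specificity, and KGOWS alone shifted by 0.5 SD. It gives 0.82/0.72 in KHAP and TSDPS and 0.67/0.86 in KGOWS.

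**4. Pooled AUC.** The 80/80 tool has a within-cohort AUC of Φ(1.683/√2) = 0.883. Pooled AUC averages Φ((shift of unimpaired − shift of impaired + 1.683)/√2) over all pairs of impaired and unimpaired participants.
- TSDPS version harder by 0.25 or 0.5 SD: 0.886.
- KGOWS or KHAP version harder by 0.25 to 0.5 SD: 0.871 to 0.880.

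The change is small and its sign depends on which version is harder.

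**5. Power to see item-by-cohort differences.** KGOWS against the other two cohorts, OR 6 in those two, 20% errors among the unimpaired, two-sided 5% Wald test. Power is about 22%, 53%, 89% and 97% for OR ratios of 1.5, 2, 3 and 4.

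**The case against.** The article does not say in so many words that ROC curves and cut-offs are pooled, or that a main effect is the only use of cohort. Naming the original and modified forms could mean an analysis per form. The list of confounders is open-ended. A registered Statistical Analysis Plan and appendices exist but are not shown, and Data harmonisation promises that "Variables of interest will be recoded to be consistent across datasets prior to combination into a single final dataset". The short scale is called a prototype and is to be validated separately.

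Part of this stands. By-version analyses may exist elsewhere, and the article does not say which items were changed, how many, or why. Non-equivalence of items is therefore a possibility, not a documented fact. But the objective places the search in the harmonised data set, adjusting for cohort only makes sense in a pooled model, and a single scale is the product. Pooling is the natural reading, and the stated method does not fit that aim. Validation in one separate cohort comes after items are chosen and cannot show performance in all three settings, so it is a partial safeguard.

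A reader might infer two stronger claims. One is that version differences, tracking prevalence, materially inflate the pooled AUC. Cohort membership alone does give an AUC of 0.57 to 0.58, but only if scores separate completely between cohorts and discriminate not at all within them. At shifts of 0.25 to 0.5 SD with no discrimination, the pooled AUC is at most 0.52, and for a working tool the change is as in step 4. The other is that cohort adjustment leaves harder items mixed in with true discrimination. Step 2 shows that in the adjusted item model it does not.

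**Conclusion.** The point holds in a limited form. On the stated method, adjusted item odds ratios are protected against differences in item difficulty but would not reveal differences in discrimination by version, and nothing extends the adjustment to the ROC curves or cut-offs. The main consequence is uneven accuracy at a common cut-off, from about 76/83 against 83/76 at 0.25 SD to 63/91 against 91/63 at 1 SD, for an assumed 80/80 tool with equal-variance normal scores. The second is that an item performing poorly in one cohort can still rank high. Pooled AUC is a minor issue. How large the version differences really are cannot be learned from the article.

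This concerns a secondary aim, and the data to address it are already in hand.

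**What to change.** In Analyses of secondary outcome:

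- Restrict short-scale candidates to items common to the three versions.
- Report each item's association by cohort, with intervals. Do not use an interaction test as a gate for selection, since power is limited (step 5).
- Estimate AUC, sensitivity and specificity within cohort and combine them by cohort-stratified ROC analysis. For any common cut-off, report how it performs in each cohort.
- Check the chosen item set by leaving out one cohort in turn.
- State that version and population effects cannot be separated, because version appears to coincide with cohort and the cohorts differ in other ways (age 60 and over in KGOWS, 45 and over in the others). Describe the planned separate-cohort validation as a partial safeguard.

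If the registered analysis plan already does this, a sentence saying so would suffice. The change is to analysis wording only and needs no new data. The price is wider intervals for cohort-specific estimates and possibly fewer eligible items.

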## Discussion

### Strengths and weaknesses

The pooled dataset brings together three Australian landmark cohort studies of dementia involving Aboriginal and Torres Strait Islander peoples with the potential to offer greater insights through enhanced statistical power. Risk and protective factors associated with dementia can be determined from the combined cross-sectional cohort of 898 participants but causality cannot be inferred. The pooled longitudinal cohort is more modest in size and contains more coarse measures of variables of interest, however, it will allow for analyses of incident dementia and cognitive impairment. We are also limited by the risk factor data available across all three cohorts. Some important omissions include physical inactivity, cognitive stimulation, social isolation, diet and adverse childhood experiences. There are also many social and cultural determinants of health which are yet to be measured and investigated in relation to dementia risk, which are likely to be important for optimising brain health and reducing dementia risk.

### Anticipated research and implications for this harmonised dataset

The 2020 Lancet Commission on Dementia Prevention, Intervention and Care suggested that at a population level, up to 40% of dementia may theoretically be preventable by eliminating certain risk factors [26]. These included less education in early life, hypertension, hearing impairment, smoking, obesity, depression, physical inactivity, diabetes, social isolation, traumatic brain injury, excessive alcohol consumption and air pollution as key risk factors in the development of dementia. Studies suggest that the preventable risk of dementia is greater in some Indigenous populations than global estimates, though risk profiles may differ between Indigenous groups [34–36] and when compared to other non-Indigenous ethnic groups [35, 37]. Greater understanding of risk and protective factors of dementia relevant to Aboriginal and Torres Strait Islander peoples may assist in preventative efforts to promote brain health and resilience over the life-course.

Risk evaluation tools are useful in primary care to identify high-risk patients and provide a framework for managing risk factors associated with chronic diseases. This has been successfully demonstrated in several fields of medicine such as cardiovascular disease (e.g. CHADs-VASC; Framingham cardiovascular risk score) and osteoporosis (FRAX; Garvan Institute Fracture Risk Calculator) [38–41]. The risk and protective factors identified from the harmonised data may allow for the development of a strength-based tool for assessment of brain health for older Aboriginal and Torres Strait Islander peoples. We envisage that this inexpensive tool would be linked to Best Practice Guidelines to provide a framework for patient education, optimise the management of conditions impacting on brain health and enhance appropriate follow-up at the primary care interface. Through the On TRACK CRE, we will translate this research with Indigenous engagement to ensure community informed and culturally safe care.

### Final conclusions

Greater understanding of risk and protective factors for dementia relevant to Aboriginal and Torres Strait Islander peoples may improve public health approaches to promote brain health across the life course. It could also improve timely and supported diagnosis of dementia and enables early interventions, minimisation of harm through de-prescribing of medications, review of comorbid conditions and discussion of future planning in culturally meaningful ways. This research aligns with community efforts to ‘Close the Gap’ and reduce disparities in rates of dementia and outcomes between Indigenous and non-Indigenous Australians.

## Data Availability

Data will not be made publicly available due to ethical requirements. External collaborators can apply to the KHAP, KGOWS and HART steering committees for further information about individual datasets for future studies.

## Abbreviations

ADL: Activities of Daily Living
AHMRC: Aboriginal Health and Medical Research Council
ATC: Anatomical Therapeutic Chemical
ANU: ADRI-Australian National University Alzheimer’s Disease Risk Index
APOE ε4: Apolipoprotein E allele 4
AUC: Area Under the Curve
AUDIT: C-Alcohol use disorders identification test for consumption
BMI: Body Mass Index
CAIDE: Cardiovascular Risk Factors Aging, and Incidence of Dementia
DSM: IV-Diagnostic and Statistical Manual-IV
CIND: Cognitive Impairment No Dementia
DSM IV: TR-Diagnostic and Statistical Manual for Mental Disorders, 4th Edition
EFST: Elderly Falls Screening Test
HART: Healthy Ageing Research Team
IRG: Indigenous Reference Group
KDS: Kilsyth Disability Scale
KHAP: Kimberley Healthy Adults Project
KICA: Kimberley Indigenous Cognitive Assessment
KICA: ADL-Kimberley Indigenous Cognitive Assessment-Activities of Daily Living
KICA: Dep-Kimberley Indigenous Cognitive Assessment-Depression Scale
KGOWS: Koori Growing Old Well Study
Let’s CHAT Dementia: Let’s CHAT (Community Health Approaches To) Dementia
mKICA: modified Kimberley Indigenous Cognitive Assessment
MCI: Mild Cognitive Impairment
MMSE: Mini-Mental State Examination
NHMRC: National Health and Medical Research Council
NSW: New South Wales
On TRACK: On TRACK (Teaching, Research And Community Knowledges)
OSF: Open Science Framework
OR: Odds ratios
ROC: Receiver Operating Characteristic
TSDPS: Torres Strait Dementia Prevalence Study
WA: Western Australia
WAAHEC: Western Australian Aboriginal Health Ethics Committee
WHO: World Health Organisation
